### Outcomes and data collection

In this pilot trial, we will note the success and viability of the trial processes, including the proportion of eligible patients and clinicians we are able to recruit and our ability to collect and analyze all outcomes in all randomized patients, i.e., to adhere to the intention to treat principle.

To assess efficacy, we will measure the effect of *OSTEOPOROSIS CHOICE *on the following outcomes: (a) patient knowledge about osteoporosis risk factors and treatment; (b) quality of the decision-making process for patient and clinician; (c) patient and clinician acceptability and satisfaction with the decision aid; and (d) rate of bisphosphonate use and adherence in at-risk women. We will survey patients and clinicians after each visit (the complete set of questions is in the **appendix) **and video record the clinical encounters to capture these outcomes. Pharmacy prescription profiles and follow-up telephone interviews will assess medication start and adherence at 6 months.

The patient questionnaire includes:

• Items about education level, annual income and health status for descriptive purposes.

• 15 items to assess patient knowledge, 13 of which refer to osteoporosis in general and the benefits and downsides of taking a bisphosphonate (9 questions about information on the decision aid, 4 questions not informed by content on the decision aid), as well as two questions about patient's personalized fracture risk and estimated risk reduction with bisphosphonates. These items were fashioned after similar items showed construct validity and responsiveness to the intervention in previous decision aid trials [14,15,28].

• 5 items using a 7-point Likert-type scale to assess the patient's perceptions of the amount, clarity and helpfulness of information, their desire to receive information about other medical treatment choices in the same way this information was delivered, and whether they would recommend the way they received information from their clinician during this visit to other patients. We have used these same items in our previous trials [15,28].

• 10 items from the Trust in Physician scale [31] and

• 16 items from the Decisional Conflict Scale [32] -- the most commonly used outcome measure in clinical trials of decision aids, which assesses the extent to which the decision was informed, consistent with values, free of pressure, and effective.

• Additional questions (see appendix) inquire about the treatment decision made during the visit and patient satisfaction with the degree of participation in the decision-making process.

The clinicians' survey, to be completed after each study visit, includes questions regarding which decision the patient made, the clinician's confidence in the patient's understanding of the information offered, and the clinician's prediction of patient action (start and adherence to bisphophonates at 6 months).

To evaluate the quality of decision-making, we will use the OPTION scale [33] on the video recordings. This scale allows an observer to quantify the extent to which clinicians are able to involve patients in the decision-making process. We have used the OPTION scale on video-recorded encounters with adequate reliability in previous studies [28,34]. Video recordings also provide information about encounter duration (using the video time stamps), fidelity of use of the tool, and difficulties and successes experienced while using the decision aid, and are the source of data for the contamination checklist described above.

We will use two methods to assess patient adherence to bisphophonates at six months. We will contact patients by telephone and measure patient self-reported adherence using the Haynes' single item adherence question ("Have you missed any of your pills in the last week?") a measure associated with a 96% specificity and 75% accuracy vs. a pill count standard [35,36]. We will also obtain patients' pharmacy records in order to objectively determine medications filled since the study visit. Using this information, we will consider a gap (time without medication) of longer than 90 days as bisphosphonate discontinuation. We will assess adherence to bisphosphonates by assessing the proportion of days covered during the 180 days after the visit, taking into account potential overlap in supply that may result when a refill comes before the estimated completion of the previous fill. We will define persistence as the number of days from the first prescription fill to the last fill in the 180 days after the visit. In this case, we will take into account overlapping supply and the number of days supplied at the last fill, truncating at 180 days after the visit [37,38]. In addition to these continous measures, we will assess and compare the proportion of patients who exhibited ≥ 80% adherence to bisphosphonates in both groups.

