### Interventions

#### Decision aid

The *OSTEOPOROSIS CHOICE *decision aid tool was developed through an iterative process and with extensive field-testing involving patients, clinicians, designers, and researchers [23,24]. This one-page decision aid provides the patient's individualized 10-year risk estimate of having a major osteoporotic fracture (clinical spine, forearm, hip or shoulder fracture). The risk is calculated using data from the patient's medical record (completed by direct query to patient or clinician as needed) and entering it into the online FRAX tool as implemented during the course of the study.

We developed three decision aids that describe the pros and cons of treatment, one for each of three categories of estimated 10-year risks of fracture: <10%, 10-30%, and >30%. At the time we designed the decision aids, there were no guidelines to orient therapeutic decisions based on fracture risk. Thus, the design team, in conjunction with patients and clinicians, arbitrarily chose these thresholds. The decision aid also shows the patient-specific absolute reduction of fracture risk with alendronate, assuming a treatment-related reduction in overall osteoporotic fracture risk of 40% [25], and the potential downsides of taking bisphosphonates.

To estimate the gastrointestinal side effects of oral bisphosphonates we reviewed the FDA-approved package insert, reports of pivotal clinical trials, and observational studies [3]. Evidence of the association between bisphosphonate use and osteonecrosis of the jaw was also evolving while we were designing the tool [26]. The estimate presented was derived from available reviews of weak evidence and expert judgment from specialist clinicians on our research team [27]. Finally, the decision aid also prompted further discussion of these issues with the question "What would you like to do? (Figure 1).

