### Randomization

A computer-generated allocation sequence will randomize patients 1:1 in a concealed fashion to control (usual care + booklet) or intervention (*OSTEOPOROSIS CHOICE *decision aid). The study coordinator will complete the following steps:

• assess the eligibility of the patient, obtain the patient's written informed consent and enroll the patient;

• access a secure study website, input patient identifiers to document patient eligibility;

• obtain from the website interface the arm of the study to which the patient is allocated;

• when the website is not available, the coordinator will contact the study statistician and a similar procedure will be used to provide concealed random allocation.

After randomization, only data analysts will remain blind to allocation. If a patient were suspected of having incorrectly enrolled, e.g., the patient is found to be ineligible after enrollment and randomization, the study coordinator will present the case to the study principal investigator ([name]) for consideration. Following existing recommendations [30], the principal investigator will decide on exclusion while unaware of any consequences of enrollment, including the patient's allocation or outcomes.

The following issues were considered in our choice[15] to randomize clinics, clinicians, or patients:

• *Randomize by clinics *- This approach would enable us to train everyone in the intervention (and control) clinics to use (or not) the decision aid. Disadvantages included the small number of available clinics, difficulty in balancing the number of participating clinicians and patients across sites, and limited ability to avoid selection bias or implement allocation concealment.

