### Statistical considerations

We have funding and plan to enroll and randomize 100 patients. While this number of patients is insufficient to reach a definitive answer about the efficacy of the decision aid and its effect on medication adherence, it is sufficient to ascertain the following differences:

• for knowledge gains, assuming that patients in the control group will be able, on average, to answer 4 of the 9 specific knowledge questions correctly, we will have 92% power to detect a ≥42.5% increase in mean knowledge (to a mean of 5.6 questions answered correctly) in the intervention group, assuming equal variances between the two arms and alpha = 0.05;

• for adherence, estimating that the 6 month adherence rate is 65% (null hypothesis), we will be powered (80%) to detect a difference (alpha = 0.05) in adherence rates of 35% (88% alternative hypothesis). To our knowledge, there is no policy- or patient-important minimum difference in adherence rates identified in the literature to otherwise guide the choice of a threshold.

The distribution of study variables will be described (using frequencies for categorical variables and measures of central tendency for continous variables) and compared using relative (relative risk) or absolute (mean differences) measures of association and their 95% confidence intervals. Because we expect a very low patient-to-clinician ratio, we do not anticipate having to use generalized estimating equations to adjust for clustering by clinician. To test hypotheses of association, we will use Wilcoxon rank-sum tests to compare medians, and Chi-square or Fisher's Exact tests to compare frequencies. All analyses are based on two-sided tests at significance level 0.05. Consistent with the intention to treat principle [39], all efforts will be placed on avoiding missing data and all patients will be analyzed in the arm to which they were randomized; participants with missing data will not be part of the analyses requiring the missing data. All analyses will be conducted using SAS (SAS Institute, Cary, NC).

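### All named comparisons are unadjusted and education is kept for description in a post-visit survey; a prespecified education- and age-adjusted knowledge estimate would be a cheap, modest gain if these covariates are prognostic

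*Protocol article*

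**What the plan says.** Under Outcomes and data collection, the patient questionnaire includes "Items about education level, annual income and health status for descriptive purposes". Its timing is set in the same section: "We will survey patients and clinicians after each visit". These items are therefore recorded after randomization and after the decision aid has been used in the intervention arm.

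Under Statistical considerations, outcomes are to be "compared using relative (relative risk) or absolute (mean differences) measures of association and their 95% confidence intervals", and for hypothesis tests "we will use Wilcoxon rank-sum tests to compare medians, and Chi-square or Fisher's Exact tests to compare frequencies". No covariate is named. The only adjustment mentioned is generalized estimating equations for clustering by clinician, which the authors do not expect to need.

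Under Randomization, "A computer-generated allocation sequence will randomize patients 1:1 in a concealed fashion"; no stratification factor is named. The planned size is 100 women, and the article says that this is too few for a definitive answer on efficacy.

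Not every characteristic waits for the survey. Age and bone mineral density are eligibility criteria. For the fracture risk estimate, the Decision aid section says: "The risk is calculated using data from the patient's medical record".

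**The concern.** In a trial of about 50 women per arm, a baseline variable that predicts the outcome can narrow the confidence interval of the treatment effect without another patient. Education and age plausibly predict a score on a factual knowledge test. The article instead gives education a descriptive role and names only unadjusted comparisons. The estimates are meant to inform a larger trial, so their precision matters.

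There is also a matter of timing. Self-reported health status is asked after women in the intervention arm have been shown their 10-year fracture risk. An answer that allocation may influence is not a clean baseline descriptor. An analysis plan written later could add a covariate, but it could not turn a post-visit answer into a pre-randomization one.

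**Working it through.** **Inputs from the article (Statistical considerations).** 100 women at 1:1, so 50 per arm; two-sided alpha 0.05; control mean 4 of 9 items; 92% power. The effect is printed as an increase of at least 42.5% (4 × 0.425 = 1.7) and also as a mean of 5.6 (difference 1.6). No SD and no R2 are given.

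**Step 1: the plan's own 92%.** Without an SD this figure can only be inverted, not reproduced. From power = Φ(δ/SE − 1.96) with SE = SD × √(2/50) = 0.2 × SD:

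- Difference 1.6: SD = 1.6 × 5 / (1.960 + 1.405) = 2.38 (2.35 by noncentral t).
- Difference 1.7: SD = 1.7 × 5 / (1.960 + 1.405) = 2.53 (2.50 by noncentral t).

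Either pair returns 92% by construction, and the results below are the same for both.

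**Step 2: effect of adjustment.** Assumptions: R2 between 0 and 0.30, and 3 covariate degrees of freedom (for example age plus education in three levels). The residual SD is SD × √[(1 − R2) × (1 + 3/94)], where 94 = 100 − 3 − 3. Effective N is 100 / [(1 − R2) × (1 + 3/94)].

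Example at R2 = 0.10, difference 1.6: residual SD = 2.38 × √(0.90 × 1.032) = 2.29; SE = 0.458; 1.6 / 0.458 = 3.49; power = Φ(3.49 − 1.96) = 93.7%.

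| Assumed R2 | Knowledge power | Power at standardised effect 0.5 | Effective N |
|---|---|---|---|
| Unadjusted | 92.0% | 69.7% | 100 |
| 0 | 91.2% | 68.3% | 97 |
| 0.02 | 91.7% | 69.2% | 99 |
| 0.05 | 92.5% | 70.5% | 102 |
| 0.10 | 93.7% | 72.8% | 108 |
| 0.20 | 95.9% | 77.8% | 121 |
| 0.30 | 97.7% | 82.9% | 138 |

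The knowledge column uses the normal formula and the 0.5 column the noncentral t. The 0.5 effect is an illustration for a less well-powered continuous scale such as Decisional Conflict; the article states no effect for that scale.

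**Step 3: simulation check.** With 10,000 runs per setting, a normal outcome, difference 1.6 and SD 2.38, the Wilcoxon test had about 90% power throughout. A linear model with one covariate gave 91.4%, 92.8%, 93.7%, 95.8% and 97.7% at R2 of 0, 0.05, 0.10, 0.20 and 0.30. This agrees with the formula.

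**The case against.** The strongest reply is that nothing here is wrong. Under concealed 1:1 randomization, unadjusted tests, mean differences and relative risks are valid. Chance imbalance is ordinary sampling error, which the planned confidence intervals already express. Simple tests are a defensible choice in a pilot, and covariate sets are often fixed in an analysis plan, which is not shown. All of this stands except the last part. The article does more than stay silent: it assigns the items a descriptive role, names the tests and fixes when the items are collected.

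Several stronger readings are tempting but unsupported:

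- **That precision is certainly being lost.** The article gives no R2 and no evidence that education or age predicts these scores. With R2 of 0.02 or less and 3 degrees of freedom, adjustment gains nothing.
- **That knowledge power starts at 89%.** This results from applying the SD of 2.5, which belongs to the 1.7 difference, to the 1.6 difference. Paired consistently, the start is the printed 92%.
- **That all patient characteristics come after the visit.** Age and bone mineral density are known beforehand.
- **That the gain extends to every outcome.** OPTION is an observer's rating of the clinician, and no reason appears why patient education should predict it. No gain is shown for Trust in Physician either. For bisphosphonate use and adherence, which are binary, the formula above does not carry over.
- **That a lost survey undermines an adjusted knowledge analysis.** Knowledge, Trust and Decisional Conflict sit in the same questionnaire, so the outcome is lost with the covariate. Earlier collection would, however, let the women lost be compared with those kept.
- **That post-visit health status biases the results.** It enters no efficacy estimate, so it cannot. It only weakens the baseline description.

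**Conclusion.** The point holds as a minor, inexpensive improvement. The stated analysis is valid and leaves some precision unused if education and age are prognostic. For R2 between 0.10 and 0.30 with 3 covariate degrees of freedom, knowledge power rises by about 2 to 6 points from 92%. Power at a standardised effect of 0.5 rises by about 3 to 13 points from 70%, and the added information is worth roughly 8 to 38 women. At R2 of 0.05 the gain is under 1 point; near zero there is a loss of about 1 point. These figures rest on the assumed R2, on an SD inferred from the printed power, and on an approximately normal score. The timing point for health status needs no such assumption, but it affects description only.

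**What to change.** 1. Record education, income and health status at the consent step, before randomization. The coordinator already meets each woman in a private room then.
2. In Statistical considerations, prespecify a linear model for knowledge with arm, education and age. Report the adjusted mean difference and its 95% confidence interval beside the unadjusted result. Do the same for Decisional Conflict if the investigators judge the covariates prognostic for it.
3. Do not adjust for health status measured after the visit.
4. Treat adjustment of OPTION, Trust in Physician and the binary bisphosphonate outcomes as optional.

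The cost is a sentence or two in the analysis section and three short items moved within the visit, with no extra patients. The downside is reliance on a simple model, and about 1 point of power if the covariates turn out not to be prognostic.

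### Persistence is defined without regard to gaps, so a woman can be both discontinued and maximally persistent; within 180 days the 90-day gap rule also cannot detect stopping from day 90 onward

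*Protocol article*

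**What the plan says.** All the relevant text is in the protocol article, Outcomes and data collection. The adherence assessment is set at six months: "We will use two methods to assess patient adherence to bisphophonates at six months". One method is a telephone question. The other uses dispensing data: "We will also obtain patients' pharmacy records in order to objectively determine medications filled since the study visit".

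Four measures are then described from the pharmacy data:

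- Discontinuation: "we will consider a gap (time without medication) of longer than 90 days as bisphosphonate discontinuation". No observation window is given in this sentence.
- Adherence: "assessing the proportion of days covered during the 180 days after the visit", with overlapping supply allowed for.
- Persistence: "We will define persistence as the number of days from the first prescription fill to the last fill in the 180 days after the visit". The adjustments are then listed: "we will take into account overlapping supply and the number of days supplied at the last fill, truncating at 180 days after the visit". Gaps between fills are not among them.
- A binary measure: "we will assess and compare the proportion of patients who exhibited ≥ 80% adherence to bisphosphonates in both groups".

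The text does not say whether a gap that counts as discontinuation also ends persistence.

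**The concern.** Discontinuation and persistence are usually read as two views of one event: when, if at all, the patient stopped. Here they are built on different rules. One is triggered by a long gap, while the other runs straight across it. The same fill history can then yield a woman who has stopped and who also has the longest possible persistence.

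The second issue is the fit between the limit and the window. A limit of 90 days is half of a 180-day follow-up. Stopping in the second half cannot produce a long enough gap before observation ends. Because the window starts at the visit and not at the first fill, women who start late lose still more observable time.

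What is at stake is the interpretation of these two measures. The Background motivates the trial partly by early discontinuation, at about 50% within one year. The Discussion says the pilot will inform a larger trial. A discontinuation rate that misses later stopping, or a persistence figure inflated by interrupted use, would be a poor planning input.

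**Working it through.** The plan gives no figure to reproduce here; the check is a day count on its definitions.

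**Inputs from the protocol article (Outcomes and data collection):** gap limit more than 90 days; 180 days after the visit for days covered and persistence; persistence from first fill to last fill plus the last supply, cut at day 180.

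**Assumptions:** The article states no supply lengths or start days, so those below are illustrative. Day 0 is the visit. A fill on day *d* with *s* days' supply lasts to day *d* + *s*. Gaps are counted only after the first fill. For the second step, the gap rule is applied within 180 days.

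**Step 1. Persistence against discontinuation.** Take 30-day fills on days 0 and 150.

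- Gap: 150 − 30 = 120 days, more than 90, so discontinued.
- Persistence: 150 + 30 − 0 = 180 days, the maximum.
- Days covered: (30 + 30)/180 = 33%.

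This conflict does not depend on the window of the gap rule, because the whole gap lies inside 180 days.

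**Step 2. What the 90-day limit can detect in 180 days.** After the last supply ends on day *e*, the final gap is 180 − *e*. It exceeds 90 only if *e* < 90. If supply covers day 90, any later gap is at most 180 − 90 = 90 days, which is not more than 90. Any gap between the first fill and day 90 is shorter than 90 days. So nobody with supply through day 90 can be classed as discontinued, whatever the fill sizes.

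For a single fill and no refill, the rule needs *d* + *s* < 90:

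- 28-day supply: flagged if filled by day 61
- 30-day supply: by day 59
- 84-day supply: by day 5
- 90-day supply: never

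**Step 3. Examples.**

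| Fills, then none | Longest gap (days) | Discontinued? | Persistence (days) | Days covered |
|---|---|---|---|---|
| 30 d on day 0; 30 d on day 150 | 120 | yes | 180 | 60/180 = 33% |
| 30 d on day 0; 30 d on day 121 | 91 | yes | 151 | 60/180 = 33% |
| 90 d on day 0 | 90 | no | 90 | 90/180 = 50% |
| 30 d on days 0, 30 and 60 | 90 | no | 90 | 90/180 = 50% |
| 60 d on day 30 | 90 | no | 60 | 60/180 = 33% |
| 30 d on day 60 | 90 | no | 30 | 30/180 = 17% |
| 30 d on day 0 | 150 | yes | 30 | 30/180 = 17% |
| 30 d on days 0 and 30 | 120 | yes | 60 | 60/180 = 33% |

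The first two rows show discontinued women with long persistence. The next four show women who stopped but are not flagged. The last two show that early stopping is detected.

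**Step 4. Other limits.** For a limit of *g* days, final stopping is visible only if supply ends before day 180 − *g*: day 150 for *g* = 30, day 135 for *g* = 45, day 120 for *g* = 60, day 90 for *g* = 90. A shorter limit moves the ceiling later but does not remove it.

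**The case against.** The strongest reply concerns the window. The 180 days are attached to days covered and to persistence; the gap sentence has no window, and the pharmacy records are described only as running from the study visit. If records extend further, the day-90 ceiling moves. This stands: the ceiling is conditional. But no longer window is given and the assessment is described as six-monthly, so 180 days is the natural reading. The conflict with persistence remains either way.

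A second reply is that persistence is a duration and not a stopped/not-stopped label, so a restart after a long interruption may legitimately give a long first-to-last span. That is fair as a description of a span. It does not help a reader who takes persistence to mean time on treatment without discontinuing, and the text does not warn against that reading. The authors may have meant persistence to end at a qualifying gap, and the article cites sources for its method, but the definition as printed runs to the last fill.

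A third reply is that a condensed article may leave operational detail elsewhere. True, but the point concerns definitions that the article does state.

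A fourth reply is that other measures capture these women. It stands in full: every woman in the table has at most 50% of days covered and fails the 80% threshold. A reader might infer that the adherence comparison is compromised. It is not, since neither days covered nor the 80% proportion uses the gap rule or the persistence definition.

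A reader might also infer a bias between arms, if the decision aid changes when women start or how much is dispensed. Nothing in the article supports that, so it remains conjecture.

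**Conclusion.** The point holds as a defect in two outcome definitions. Applied as written, they can class one woman as discontinued and give her the maximum persistence of 180 days with 33% of days covered. That follows from the printed text alone, with fill dates chosen for illustration.

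The day-90 ceiling holds if the gap rule is confined to 180 days after the visit, an inference from the six-month assessment. Under that reading the rule is insensitive to later stopping and to late starters. It is not void: one or two consecutive 30-day fills from day 0 followed by stopping are flagged.

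The number of women affected cannot be estimated, because the article gives no supply lengths and says (Discussion) that the proportion starting a new medication is often unknown beforehand. The impact is limited to discontinuation and persistence in a 100-patient pilot. The power statements concern knowledge and the adherence rate, not these measures. The definitions should be corrected, but this is no reason to doubt the trial's main comparisons.

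**What to change.** Three changes to the outcome definitions:

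1. Define persistence as days from first fill to the end of supply before the first gap exceeding the discontinuation limit, truncated at day 180. The woman with fills on days 0 and 150 then has 30 days of persistence, in line with her classification.
2. State the observation window for the gap rule.
3. If that window is 180 days, either report discontinuation also with shorter permissible gaps (for example 30, 45 and 60 days) as sensitivity values, or describe the 90-day result as detecting only stopping before day 90.

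These changes need a few sentences and use the pharmacy data already planned. The downside is that shorter gaps may label some temporary lapses as discontinuation, which is why they are proposed as sensitivity values; each still has its own ceiling (Step 4). Extending the pharmacy extraction to 270 days (180 + 90) is optional. It would let the 90-day rule observe stopping up to about day 180, but it needs a further 90 days of records.

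### Persistence is counted from the first fill but cut at 180 days after the visit, with no censoring stated, so it mixes delay in starting with stopping

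*Protocol article*

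**What the plan says.** Under Outcomes and data collection, the protocol article derives three things from the pharmacy records.

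- **Discontinuation:** "we will consider a gap (time without medication) of longer than 90 days as bisphosphonate discontinuation".
- **Adherence:** "proportion of days covered during the 180 days after the visit", also split at 80% to compare "the proportion of patients who exhibited ≥ 80% adherence to bisphosphonates in both groups".
- **Persistence:** "persistence as the number of days from the first prescription fill to the last fill in the 180 days after the visit", taking into account overlapping supply and "the number of days supplied at the last fill, truncating at 180 days after the visit".

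The article groups adherence and persistence as continuous measures. For such measures, Statistical considerations says "we will use Wilcoxon rank-sum tests to compare medians"; chi-square or Fisher's exact tests are for frequencies. No time-to-event method or censoring is mentioned. Under Inclusion criteria, women are not on bisphosphonates at entry, so every woman's first fill comes after enrolment and its date can vary.

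**The concern.** A persistence measure should say how long a woman stays on treatment once she has started. Here the start of the count moves with the woman while its end is tied to the visit, so a late starter has less time in which persistence can be observed. A woman still supplied at the end has not stopped, yet her value enters the rank test alongside values that do end in stopping.

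What is at stake is the interpretation of a between-arm difference. The decision aid prompts the patient to consider what she would like to do, so it might change how soon she fills a prescription. If it did, the arms could differ on persistence with identical stopping. The article says the results will inform the design of a larger trial, and a delay effect read as a stopping effect would misinform that design.

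**Working it through.** The article gives no figure for persistence, so there is none to reproduce.

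**Ceiling.** Let d be the day of first fill, in days after the visit. Persistence = min(end of last supply, 180) − d, so the maximum is 180 − d.

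| First fill, supply never broken | Persistence |
|---|---|
| day 0 | 180 |
| day 40 | 140 |
| day 61 | 119 |
| day 91 | 89 |
| day 100 | 80 |

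All of the 40-day difference between the first two women is delay in starting.

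**Can a woman who never stops score below one whose supply ended?** Yes. A day-0 starter whose supply ends on day 120 scores 120, above the 119 of a day-61 starter with unbroken supply. That first woman has a gap of 180 − 120 = 60 days by the end of the window, so she is not a discontinuer under the 90-day rule. A day-0 starter with a final gap over 90 days has supply ending no later than 180 − 91 = day 89 and scores at most 89. For a continuous user to score less, 180 − d < 89, so d > 91.

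**The gap rule is not used in persistence.** With 30-day fills (an assumption) on days 0 and 150, persistence is min(150 + 30, 180) − 0 = 180 days. The gap runs from day 30 to day 150, or 120 days, which the article's own rule calls discontinuation.

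**Possible size between arms.** Assumptions:

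- The stopping rate is the same in both arms: 50% within one year (Background). Stopped by 180 days after starting: 1 − 0.5^(180/365) = 0.29.
- Delay D to first fill is exponential. The means are assumed, because the documents give none.
- Persistence = min(stopping time T, 180 − D), among women who fill within the window.
- Two-sided Wilcoxon test at 0.05. With 100 women randomised 1:1, 50 starters per arm is an upper bound that requires every woman to start.

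| Mean delay (days) | Rejections, 20 starters per arm | Rejections, 50 starters per arm |
|---|---|---|
| 30 v 30 | about 5% | about 5% |
| 10 v 15 | about 9% | about 16% |
| 10 v 20 | about 20% | about 38% |
| 10 v 30 | about 37% | about 75% |

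With 10 v 30 days, mean persistence is about 145 v 130 days although stopping is identical. These are simulation results and can move by a few points between runs.

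**The 80% mark.** 0.80 × 180 = 144 covered days. A first fill on day 36 can give 144/180 = 80.0%; day 37 gives at most 143/180 = 79.4%. If the window is numbered from day 1 and the fill day is counted, the limit is day 37.

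**The case against.** The case on the other side is substantial, and much of it stands.

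- **Reversals.** A reader might infer that late starters who never stop are generally ranked below women who quit early. The documents do not support that. Against a quitter under the 90-day rule, a first fill after about day 91 is needed. Under exponential delays with means of 10 and 30 days, only about 0.01% and 5% of women start that late.
- **The 80% split.** A reader might also call it an error that a woman first filling after day 36 cannot reach 80%. It is not. The article openly takes coverage over the 180 days after the visit, which gives every randomised woman the same window and fits the intention-to-treat aim. It is a coherent joint measure of starting and being covered.
- **Validity of the test.** With equal delays the rejection rate stays at about 5%. The rejections above reflect a real difference in time on drug within the window, and the dispute is over calling it persistence. The unequal delays have no source in the documents.
- **Reach.** Start of medication is assessed separately, self-reported adherence at six months does not use this window, and the article says the sample is too small for a definitive answer. The adherence results as a whole are therefore not made uninterpretable.
- **Unseen analysis plan.** The Wilcoxon sentence is general, and a separate plan might handle women still supplied at day 180.

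The last point does not remove the concern. The article itself fixes the two anchors and the truncation, and it lists persistence as a continuous measure. Following that text gives a ceiling that depends on the start date. Nor does the ceiling need a quitter to matter, as the two continuous users at 180 and 140 show.

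**Conclusion.** The point holds for the persistence definition and its analysis, and only for those. The ceiling of 180 minus the first-fill day follows directly from the article's wording, and a woman still supplied at day 180 is given a completed value. Persistence as defined therefore mixes delay in starting with stopping.

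Whether this biases the comparison depends on whether delay differs between arms, which the documents do not tell us. With equal delay there is no bias. Under the stated assumptions, the chance of a significant persistence result with identical stopping runs from about 9% (10 v 15 days) to 37% (10 v 30 days) with 20 starters per arm. With 50 per arm it runs from about 16% to 75%, and the Discussion warns that women leaving with a prescription may be far fewer than those randomised. It affects one pharmacy measure in a pilot and is worth correcting because the correction is cheap.

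**What to change.** 1. Analyse persistence as time from first fill to discontinuation, with women still supplied at day 180 censored there, using Kaplan-Meier curves and a log-rank test.
2. Reconcile discontinuation in that analysis with the 90-day gap rule stated alongside it. At present a woman can have a gap over 90 days and still score 180. The wording should also cover a woman whose supply ends on day 90 or later, since a gap over 90 days cannot be seen within the window for her.
3. Report time from visit to first fill as a separate outcome, so that a difference in starting is visible as such.
4. Leave coverage over the 180 days from the visit, and its 80% split, as planned. Add one sentence saying that it measures starting and coverage jointly, and that 80% cannot be reached after a first fill past day 36 (37 if the fill day is counted).

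The cost is revised wording and a little programming on the same pharmacy records. Late starters add little follow-up, so precision is slightly lower. The persistence comparison is among starters only, so it is not a comparison of the groups as randomised and should be labelled accordingly. Censoring also assumes that, within an arm, late starters stop at the same rate as early starters.
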